# High‐intensity training as a novel treatment for impaired awareness of hypoglycaemia in type 1 diabetes [HIT4HYPOS]: Protocol for a randomized parallel‐group study

**DOI:** 10.1002/edm2.166

**Published:** 2020-07-21

**Keywords:** adrenaline, behaviour, counterregulation, diabetes, exercise, habituation, hypoglycaemia, impaired awareness

## Abstract

**Aim:**

This pilot study aimed to investigate whether a 4‐week programme of intermittent high‐intensity training (HIT) will improve counterregulatory responses and improve hypoglycaemia awareness in adults with type 1 diabetes who have been exposed to recurrent hypoglycaemia.

**Methods:**

Adults with type 1 diabetes who have been exposed to recurrent hypoglycaemia will be recruited from NHS Tayside, Scotland. All participants have a 4‐week run‐in period to optimize glycaemic control and to receive instruction in hypoglycaemia avoidance using insulin dose adjustment and real‐time continuous glucose monitoring (CGM). Following this, they will undergo a baseline 90‐minute hyperinsulinaemic hypoglycaemic clamp to assess symptomatic, cognitive and hormonal counterregulatory responses. Subsequently, participants will be randomized in a parallel‐group design to either undergo a 4‐week intervention with HIT or to no exercise with both groups using CGM throughout and receiving additional advice on hypoglycaemia avoidance. Participants in the HIT arm of the trial will be instructed to exercise 3 times a week on a cycle ergometer and asked to achieve ≥ 90% max heart rate during each period of exercise. On completion of the intervention period, all subjects then undergo a second matched hyperinsulinaemic hypoglycaemic clamp study.

**Discussion:**

This pilot study will determine whether high‐intensity exercise may offer a novel approach to restore hypoglycaemic awareness in type 1 diabetes (International Standard Randomised Controlled Trials No: ISRCTN15373978).

## INTRODUCTION

1

Impaired awareness of hypoglycaemia (IAH) is defined as ‘a diminished ability to perceive the onset of acute hypoglycaemia’.^1^ IAH affects 20%‐25% of all people with type 1 diabetes, and of concern, the incidence of IAH has not changed in the last 2‐3 decades despite the introduction of insulin analogues and improved insulin delivery systems.^2^ In people with type 1 diabetes, IAH increases the risk of severe hypoglycaemia (defined as the need for external assistance to recover) by up to sixfold.^3^ IAH is an acquired abnormality that is essentially a complication of insulin therapy; it should be placed alongside retinopathy, neuropathy and nephropathy as its morbidity and mortality can be just as serious and disabling. The underlying mechanisms that lead to the development of IAH are unclear; however, it has been well established in multiple studies in people with and without type 1 diabetes that IAH can develop by inducing one or more episodes of experimentally induced hypoglycaemia.^4^ In addition, the greater the frequency of incidence exposure to hypoglycaemia, the greater the degree of suppression of symptomatic and hormonal counterregulatory responses (CRR), a process that can be reversed through strict hypoglycaemia avoidance.^5^, ^6^, ^7^

Habituation is a form of adaptive memory that develops in many organisms in response to a repeated, often stressful stimulus.^8^ Habituation is defined as a ‘reduction of the psychological, behavioural or physiological response to a stimulus as a result of repeated or prolonged exposure’.^8^, ^9^ This definition of a habituated response is consistent with the changes in CRR evoked by repeated hypoglycaemia in people with type 1 diabetes where there is also a progressive reduction or loss of psychological (anxiety), behavioural (food seeking) and physiological (symptom and hormonal) CRR.^8^, ^9^, ^10^ This suggests the hypothesis that IAH develops through habituation to repeated hypoglycaemia. To test this hypothesis, we recently conducted two proof‐of‐concept studies in rodents^11^ and humans.^12^ In these two studies, we sought to determine whether IAH could be at least temporarily improved by the introduction of a novel stress stimulus, a phenomenon referred to as dishabituation and a key feature of habituation. Consistent with our hypothesis, we reported that a single 20‐minute programme of high‐intensity exercise significantly augmented the CRR to subsequent hypoglycaemia in both the rodent model^11^ and humans with long‐duration type 1 diabetes and IAH.^12^ However, while we have demonstrated that a single episode of HIT can at least temporarily improve the counterregulatory defect induced by recurrent hypoglycaemia, it remains possible that the effect is (a) not sustained or (b) individuals may over time adapt to the novel dishabituating stimulus.

## AIM

2

To investigate whether a 4‐week programme of intermittent high‐intensity exercise will improve counterregulatory responses and restore hypoglycaemia awareness in adults with T1D and IAH beyond the benefits that may be achieved through optimal treatment.^13^

## PARTICIPANTS AND METHODS

3

### Study design

3.1

This is a randomized, parallel‐group, single‐centre pilot study conducted in NHS Tayside, Scotland. Up to 32 participants will be randomized 1:1 to intervention; 4‐week programme of intermittent high‐intensity exercise and continuous glucose monitoring, or control; and 4 weeks of continuous glucose monitoring alone.

### Study population

3.2

Impaired awareness of hypoglycaemia (Gold score ≥4 or Modified Clark score ≥4 or DAFNE hypoglycaemia awareness rating 2 or 3) and/or evidence of recurrent hypoglycaemia (defined as ≥2 blood glucose or flash glucose readings of <4.0 mmol/L a week, based on long‐term history and up to 90 days flash glucose monitoring or CGM).

Inclusion criteria were as follows:
Adults ≥18 and ≤55 yearsType 1 diabetes
>5 years' disease durationHbA1c < 75 mmol/LOn intensive insulin therapy (CSII or MDI)

Exclusion criteria were as follows:
Competitive sportsman/womanHistory of significant heart diseaseIschaemic heart disease, congestive cardiac failure or cardiac surgeryTreatment with beta‐blockersTreatment with oral steroids within the last 6 monthsAnaemia (Hb < 120 g/L for women, Hb < 130 g/L for men)Renal impairment (eGFR < 60)History of significant lung disease—that limits exerciseHistory of significant neurological disease—those with a history of seizures second to hypoglycaemia must be seizure‐free for 12 months prior to consent.High‐risk foot diseasePrevious amputation of toes/foot/legPregnant women or breastfeeding mothersParticipation in HIT or equivalent in past 6 monthsPhysical ability that may limit exerciseInability to give consent

## METHODS

4

### Screening

4.1

Potential participants will be identified using the Scottish Diabetes Research Network (SDRN) and from the diabetes outpatient clinics in NHS Tayside, Scotland. They will be invited to attend a screening visit where informed written consent will be given and eligibility confirmed. This will involve a review of their medical history, recent blood results and flash glucose monitoring if applicable and completion of three questionnaires: Gold et al,^14^ Clarke et al^15^ and DAFNE,^16^ to determine degree of subjective hypoglycaemia awareness.

After entering the study, participants will be randomized to either the HIT programme (Figure 1) along with CGM (HIT&CGM) or CGM alone (control), in conjunction with advice on hypoglycaemia avoidance (Figure 2).

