### Run‐in period

4.2

All participants will then enter an initial 4‐week run‐in period. During this time, their glycaemic control will be optimized through insulin dose adjustment, review of carbohydrate counting/ratios and instructions on hypoglycaemia avoidance. This will be done via a phone call or email once a week by the Clinical Research Fellow (CRF).

During the 4‐week run‐in period, there will be one study visit (visit 2), which takes place in week 1 or 2. During this visit, all participants will be taught how to fit the real‐time continuous glucose monitor (CGM) (Dexcom G6; Dexcom) and shown how it works.

For those participants in the HIT&CGM group, during visit 2 medical history will be detailed and participants will undergo clinical examination. An electrocardiogram and vital signs including blood pressure and heart rate will be checked as a safety measure. Participants will undergo an assessment of their baseline fitness by carrying out a VO_2_ peak and heart rate peak assessment on a cycle ergometer (Corival, Lode; Metamax 3B, CORTEX Biophysik). The VO_2_ peak will be performed as an incremental maximum fitness test; 2 minutes at rest to ensure accurate readings followed by 5‐minute warm‐up at 25w, cycling at a cadence of 40‐60RPM. The incremental protocol will then begin at 35w, increasing by 15w per minute while maintaining a cadence of approximately 60RPM. Rating of perceived exertion (RPE) will be assessed every minute during the test using the Borg scale.^17^ The test will continue until VO_2_ peak is reached. Three of the following four criteria need to be satisfied:
RPE ≥ 18Respiratory exchange ratio >1.1Volitional fatigueMaximum estimated heart rate (220‐age)

The peak heart rate reached will be used to design the HIT programme for each participant. Participants will be given standard advice regarding insulin dose adjustments prior to and following the VO_2_ peak assessment.^18^

This visit will take place during the first 2 weeks of the run‐in period to allow any effect from VO_2_ max and heart rate peak assessment to have worn off.

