### Randomization

4.8

The randomization involved will relate to which intervention group participants are allocated to (HIT&CGM or CGM alone (control)). Randomization will be carried out by an independent individual, at the University of Dundee. Randomization will be done in a GCP‐compliant manner using http://www.randomization.com/.

Randomization will be carried out using a validated Web‐based block randomization generator to ensure that an equal number of participants are assigned to each intervention at baseline. Once the randomization has taken place, the allocation list will be concealed from the CI and CRF until the recruit has been consented. The CRF will be informed of the intervention allocation and will inform the participant once they have consented to take part in the study.

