### Statistical methods

5.2

For the primary and secondary end points, a mixed model will be used adjusting for baseline as a covariate. *P* < .05 will be considered statistically significant. Statistical analyses will be conducted using IBM SPSS Statistics 22 software.

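### The abstract randomizes after the baseline clamp but the body randomizes and discloses allocation at consent, so the baseline covariate is measured after known allocation

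*Protocol article*

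**What the plan says.** The protocol article gives two orders of events.

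- **Abstract, Methods.** The 4-week run-in comes first, then the baseline hypoglycaemic clamp, and then: "Subsequently, participants will be randomized in a" parallel-group design.
- **Section 4.1 (Screening).** After consent and the eligibility check: "After entering the study, participants will be randomized to either the HIT programme" with CGM, or to CGM alone.
- **Section 4.2 (Run-in period).** The next step is: "All participants will then enter an initial" 4-week run-in. The clinical research fellow contacts everyone weekly about insulin adjustment and avoiding hypoglycaemia. Visit 2, in week 1 or 2, has a part for one arm only: "For those participants in the HIT&CGM group, during visit 2 medical history will be detailed", with examination, ECG and an incremental maximal test ("Participants will undergo an assessment of their baseline fitness by carrying out a" VO2 peak test).
- **Section 4.3.** The baseline clamp is visit 3, at the end of the run-in.
- **Section 4.8 (Randomization).** The list is concealed until consent. After that: "The CRF will be informed of the intervention allocation and will inform the participant once they have consented to take part in the study".
- **Section 5.2 (Statistical methods).** For primary and secondary endpoints, "a mixed model will be used adjusting for baseline as a covariate".

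**The concern.** Adjusting for baseline is safe in a randomized trial because allocation cannot influence a value measured before it. That protection is lost if the value is measured after the arm is known. A shift in the visit 3 adrenaline response caused by allocation would then enter the covariate and pass, through the regression slope, into the primary contrast.

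The text offers three routes to such a shift:

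- Participants know their arm for the four weeks before the clamp and may change their behaviour.
- The fellow who gives the weekly insulin and avoidance advice also knows the arm. The Introduction says that suppressed counterregulation can be reversed by strict avoidance of hypoglycaemia.
- Only the HIT arm has a maximal exercise test before the clamp. The Introduction reports that a single 20-minute bout of high-intensity exercise raised the response to later hypoglycaemia.

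There is also a consequence for missing data. Someone who leaves during the run-in has not been randomized under the abstract's order. Under the body's order, that person is a randomized participant with no baseline value, in a trial of at most 32.

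**Working it through.** **Step 1: which order is operative.**

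| Step | Abstract | Sections 4.1 to 4.3 and 4.8 |
|---|---|---|
| 1 | Run-in | Consent, randomization, disclosure to fellow and participant |
| 2 | Baseline clamp | Run-in, with HIT-only testing at visit 2 |
| 3 | Randomization | Baseline clamp (visit 3) |
| 4 | Intervention | Intervention |

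Both columns cannot be true. HIT-only procedures in run-in week 1 or 2 are impossible unless allocation is known by then, so the body's order is the one the trial would follow. Figure 2, the flow diagram, is not shown and could not be checked.

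**Step 2: spacing of the HIT-only test.** The test falls between day 0 and day 14 of a 28-day run-in. The gap to the clamp is about 28 − 14 = 14 days to 28 − 0 = 28 days.

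**Step 3: how a shift would pass into the contrast.** The protocol states no effect size, SD, correlation or power, so there is no figure to reproduce, and all values here are assumptions in SD units. Let G be 1 for HIT and 0 for control, B the baseline that would have been seen without knowledge of the arm, τ the true effect, and β the slope of visit 8 on visit 3.

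- Observed baseline: B_obs = B + dG
- Visit 8: Y = βB + τG + pdG + error, where p is the fraction of the shift that persists to visit 8
- Substituting B = B_obs − dG: Y = βB_obs + [τ + (p − β)d]G + error

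The adjusted contrast is therefore biased by (p − β) × d.

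- No persistence (p = 0): smallest −0.5 × 0.1 = −0.05 SD, middle −0.6 × 0.25 = −0.15 SD, largest −0.7 × 0.5 = −0.35 SD.
- Persistence equal to the slope (p = β): zero.
- Full persistence (p = 1): smallest (1 − 0.7) × 0.1 = +0.03 SD, largest (1 − 0.5) × 0.5 = +0.25 SD.

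These signs are for a shift that raises the HIT baseline. They reverse if the control baseline is the one raised.

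**Step 4: simulation of the no-persistence case.** Settings: 16 per arm, linear model adjusted for observed baseline, two-sided 5% (sidedness is assumed), 8,000 runs per setting.

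| Correlation | Shift d (SD) | Type I error | Power for a true 0.8 SD effect |
|---|---|---|---|
| 0.5 | 0 | 0.046 | 0.70 |
| 0.5 | 0.25 | 0.068 | 0.55 |
| 0.5 | 0.5 | 0.119 | 0.39 |
| 0.7 | 0 | 0.053 | 0.85 |
| 0.7 | 0.25 | 0.098 | 0.65 |
| 0.7 | 0.5 | 0.246 | 0.38 |

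When allocation is released after visit 3, d = 0 by design, and the simulated bias is about zero (−0.004 and 0.001 under no effect).

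**The case against.** The strongest reply is that the body is internally consistent, one abstract sentence is the outlier, and nothing shows a shifted baseline. Section 4.2 gives both arms the same run-in contact and monitoring. Section 4.3 postpones a clamp if significant hypoglycaemia occurred in the preceding 24 hours. The outcome is a laboratory measurement. Section 4.2 also places the exercise test in the first two weeks expressly so that its effect can wear off. This is, moreover, an unpowered pilot that already allows for dropout.

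Much of this stands, and it limits what may be claimed. Four stronger readings are tempting but unsupported:

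- **That the baseline is in fact biased.** The documents show an opportunity for a shift. They do not indicate unequal advice by arm.
- **That allocation concealment or a blind has failed.** Section 4.8 hides the list until consent, so concealment at enrolment is intact. The trial is open, so there is no blind to break. The defect is the timing of disclosure relative to the baseline measurement.
- **That the trial is biased against HIT by a known amount.** A negative bias follows only if HIT raises the baseline and little of the shift persists. Weekly CGM-based advice continues in both arms through the intervention (section 4.4), so effects of coaching and behaviour may well persist.
- **That the exercise test contaminates the baseline.** The 14 to 28 days of spacing reduce that route. Section 6.2 says the duration of the intervention's effect is unknown. That concerns the full programme, so it neither proves nor excludes carry-over from one test.

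The reply does not remove the point. The spacing addresses one route only. Knowledge of the arm, advice from an informed fellow, and run-in losses remain. Pilot status does not excuse two incompatible accounts of when randomization happens.

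**Conclusion.** The contradiction is certain on the text. Under the body's order, the covariate in section 5.2 is a post-allocation measurement, which follows directly from sections 4.1, 4.2, 4.3 and 4.8. Whether it matters numerically cannot be settled from the documents. Under assumed slopes of 0.5 to 0.7, assumed shifts of 0.1 to 0.5 SD and no persistence, the adjusted contrast would be off by 0.05 to 0.35 SD. With persistence, the bias can vanish or change sign. These figures illustrate sensitivity and do not estimate bias in this trial. The case for correction rests on the sequence itself: it opens an avoidable route to bias in the primary comparison, and a shift cannot be separated from chance imbalance once the data are in.

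**What to change.** Bring the abstract and sections 4.1, 4.2 and 4.8 onto one sequence, and check Figure 2 against it.

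**Preferred: the abstract's sequence.** The independent person may generate the list at any time, but each allocation is released to the fellow and the participant only after that participant has completed visit 3. The HIT-specific preparation takes place between visit 3 and the first HIT session. Visit 3 is then a true baseline, and run-in losses occur before randomization.

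Cost: the preparation visit moves from run-in week 1 or 2 to after week 4, about 2 to 4 weeks later. It must be fitted in before the programme starts, because section 4.2 uses its peak heart rate to design the programme. No extra patients or procedures are needed. Testing everyone before visit 3 would also equalize the arms, but it adds a maximal test, ECG and examination for up to 16 controls and leaves early disclosure in place.

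**If the body's order is kept.** Correct the abstract, describe visit 3 as a post-randomization measurement, and add an analysis of the primary endpoint that does not condition on it, either unadjusted or adjusted for screening variables recorded before allocation. That analysis estimates the effect of allocation as a whole, including anything that happens in the run-in. It costs precision: at 16 per arm, 80% power and two-sided 5%, the detectable effect is about 1.02 SD unadjusted. With baseline adjustment at an assumed correlation of 0.6 it is 1.02 × √(1 − 0.36) ≈ 0.82 SD.

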**FIGURE 1 edm2166-fig-0001:**

High‐intensity training programme

**FIGURE 2 edm2166-fig-0002:**
[figure not shown]
Study flow diagram

### Run‐in period

4.2

All participants will then enter an initial 4‐week run‐in period. During this time, their glycaemic control will be optimized through insulin dose adjustment, review of carbohydrate counting/ratios and instructions on hypoglycaemia avoidance. This will be done via a phone call or email once a week by the Clinical Research Fellow (CRF).

During the 4‐week run‐in period, there will be one study visit (visit 2), which takes place in week 1 or 2. During this visit, all participants will be taught how to fit the real‐time continuous glucose monitor (CGM) (Dexcom G6; Dexcom) and shown how it works.

For those participants in the HIT&CGM group, during visit 2 medical history will be detailed and participants will undergo clinical examination. An electrocardiogram and vital signs including blood pressure and heart rate will be checked as a safety measure. Participants will undergo an assessment of their baseline fitness by carrying out a VO_2_ peak and heart rate peak assessment on a cycle ergometer (Corival, Lode; Metamax 3B, CORTEX Biophysik). The VO_2_ peak will be performed as an incremental maximum fitness test; 2 minutes at rest to ensure accurate readings followed by 5‐minute warm‐up at 25w, cycling at a cadence of 40‐60RPM. The incremental protocol will then begin at 35w, increasing by 15w per minute while maintaining a cadence of approximately 60RPM. Rating of perceived exertion (RPE) will be assessed every minute during the test using the Borg scale.^17^ The test will continue until VO_2_ peak is reached. Three of the following four criteria need to be satisfied:
RPE ≥ 18Respiratory exchange ratio >1.1Volitional fatigueMaximum estimated heart rate (220‐age)

The peak heart rate reached will be used to design the HIT programme for each participant. Participants will be given standard advice regarding insulin dose adjustments prior to and following the VO_2_ peak assessment.^18^

This visit will take place during the first 2 weeks of the run‐in period to allow any effect from VO_2_ max and heart rate peak assessment to have worn off.

### Experimental Hypoglycaemia: Hyperinsulinaemic hypoglycaemic clamp study

4.3

At the end of the 4‐week run‐in period, participants will return to the Clinical Research Centre for visit 3 where they will undergo a hyperinsulinaemic hypoglycaemic clamp.^19^ They will have been fasted from mid‐night (drinking clear fluids only). CGM data will first be analysed to ensure no significant hypoglycaemia (<3.0 mmol/L for ≥20 minutes)^20^, ^21^ in the preceding 24 hours. If there is evidence of hypoglycaemia, the study will be postponed and the visit repeated. If there is no evidence of hypoglycaemia, each participant will then undergo a controlled 90‐minute hyperinsulinaemic hypoglycaemic (2.5 mmol/L) clamp study.

In this procedure, insulin (0.3 U/mL) is infused at 50 mL/h for priming purposes until the blood glucose drops to below 7 mmol/L, after which a rate of 1.5 mU/kg/min will be maintained for the duration of the clamp. 20% dextrose is simultaneously infused at a variable rate (Infusomat Space; B. Braun Medical Ltd) based on frequent (every 5 minutes) bedside plasma glucose measures (Biosen C‐Line GP+; EKF diagnostics), to maintain blood glucose at predetermined levels. In this study, euglycaemia (glucose target 5.0 mmol/L) is initially achieved and maintained for the first 30 minutes of the glucose clamp study, and subsequently, blood glucose will be reduced over 30 minutes to a target plasma glucose level of 2.5 mmol/L, which is then maintained for a further 60 minutes before glucose levels are returned to the euglycaemic range.

Blood samples will be taken every 30 minutes during the hyperinsulinaemic euglycaemic and hypoglycaemic clamp (*t* = −30, 0, 30, 60, 90 minutes). Glucose, lactate, glucagon, adrenaline, noradrenaline, insulin and cortisol will be measured.

In addition, at each 30‐minute time point (*t* = −30, 0, 30, 60, 90 minutes) participants' cognitive function will be assessed using the Digit symbol substitution test (DSST^22^) and 4‐choice reaction time test (4CRT^23^). The Edinburgh Hypoglycaemia Symptom (EHS^24^) score will be used to assess symptom awareness at each of these time points. At the start of the hyperinsulinaemic hypoglycaemic clamp, participants will be asked to complete the World Health Organisation—Five Well‐Being Index^25^ (WHO‐5) as a measure of well‐being.

Blood samples will be centrifuged and decanted into microtubes, which will be stored at −80°C. When the study has been completed, serum and plasma samples will be transferred to the Biomarker Core Laboratory at the University of Dundee for processing.

